#### Manual chest compression arm

The control arm will receive resuscitation according to the Resuscitation Council (UK) and JRCALC Advanced Life Support Guidelines.

#### Guidelines change in 2010

The International Liaison Committee for Resuscitation and European Resuscitation Council (UK) will publish new resuscitation guidelines on 18^th ^October 2010. There is likely to be a delay before these are incorporated into clinical practice. The LUCAS-2 and manual chest compression protocols will be updated to coincide with the adoption of the new guidelines in the respective ambulance services. A subgroup analysis will be undertaken to compare treatment effects of LUCAS-2 before and after introduction of the new guidelines.

### Data Collection

Data up to admission to hospital will be extracted from routinely collected ambulance service data, and will be supplied to the trial database in anonymised form. Local Register Offices will be contacted by ambulance services after each individual's cardiac arrest, to verify whether the participant is alive and to ensure that communications about participation in the follow-up are not sent to deceased individuals. If patients have died, the date and location of death will be recorded. Trial participants will be flagged on the NHS Central Register so that later deaths will be notified to the trial.

#### Follow-up

Where consent is given, surviving participants will be followed up approximately 3 months after their cardiac arrest, by a home visit from a study research nurse or paramedic. At this visit the quality of life measures will be completed, details of ICU and hospital discharge dates will be collected, and an assessment of CPC score made.

The second follow-up visit at 12 months will include quality of life, anxiety and depression (HADS), post-traumatic stress (PCL-C) and Mini-Mental State Examination (MMSE). Health service and social care resource use will be recorded by participants at the 3 month and 12 month follow-up.

#### Serious Adverse Events (SAEs) and Serious Adverse Device Effects (SADEs)

SAEs and SADEs will be reported to the trial co-ordinating centre if they fulfil the criteria for seriousness, they are potentially related to trial participation, and they are unexpected i.e. the event is not an expected occurrence for patients who have had a cardiac arrest.

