### Outcome Measures

The primary outcome for the trial is survival to 30 days post cardiac arrest. Secondary outcomes are: survival of event (sustained return of spontaneous circulation (ROSC) to arrival at hospital); survival to hospital discharge and to 12 months; health related quality of life at 3 and 12 months (measured by SF12 and EQ-5D); neurologically intact survival to 3 months (survival with Cerebral Performance Category (CPC) score 1 or 2); cognition at 12 months (Mini Mental State Examination (MMSE); anxiety and depression at 12 months (Hospital Anxiety and Depression Scale (HADS)); post traumatic stress at 12 months (PTSD civilian checklist (PCL-C)); hospital length of stay; intensive care length of stay.

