### Sample Size Required

We aim to detect, with 80% power, an increase in the incidence of survival to 30 days from 5% in the control arm to 7.5% in the LUCAS arm (a risk ratio of 1.5). The number of LUCAS clusters (vehicles) is limited by the number of devices available, but because control clusters (vehicles) do not require any specific equipment, we can include more control clusters than LUCAS clusters in the trial (see figure 1). Detection of the specified difference with a randomisation ratio of 1:2 and a cluster size of 15 requires 82 LUCAS and 163 control clusters (3675 participants in total). The primary outcome will be determined for close to 100% of trial participants, so there is no adjustment for losses of individual patients.

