### Statistical Analysis

All analyses will be by intention to treat, and all estimates will be adjusted to account for the cluster randomised design. Dichotomous outcomes (survival to 30 days, hospital discharge, 3 months and 12 months, and neurologically intact survival) will be presented as risk ratios and 95% confidence intervals. Survival will also be analysed as a time to event outcome, using survival analysis, with adjustment for clustering and important covariates. Results will be presented using hazard ratios and their 95% confidence intervals. Other time to event outcomes (duration of hospital and ICU stay) will be analysed in the same way. Continuous outcomes (quality of life, anxiety and depression, cognition and post traumatic stress) will be analysed by multi-level linear regression, with adjustments for important covariates. The results will be presented as the difference in means between the groups and its 95% confidence interval. CPC score will be analysed by multi-level ordinal logistic regression[21] and the results will be presented using odds ratios and their 95% confidence intervals. Reporting of analyses will follow CONSORT guidelines for the reporting of cluster randomised trials[22]. A detailed analysis plan will be drawn up by the study statisticians and approved by the DMC.

Four pre-specified subgroup analyses will be conducted to conform with Utstein recommendations: witnessed cardiac arrest versus not witnessed; bystander CPR versus no bystander CPR; type of initial rhythm (VF/VT; PEA; asystole); presumed cardiac aetiology of cardiac arrest. Subgroup analyses will use statistical tests of interaction [23]. In addition, we will model the effects of age and the time interval from the 999 call to arrival of the trial vehicle on the effects of the LUCAS-2 intervention, using logistic regression analyses.

Interim analyses will be conducted at least once per year during recruitment and supplied confidentially to the DMC, who will consider the results and make recommendations to the Trial Steering Committee (TSC) about continuation of recruitment or any modification to the trial that may be necessary.

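### The expectedness test for safety reporting also applies to serious device effects and is judged against cardiac-arrest patients, so serious non-fatal LUCAS-2 effects of a familiar kind need not be reported

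*Protocol article*

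**What the plan says.** The section on SAEs and SADEs in the protocol article is a single sentence that covers both event types. It opens: "SAEs and SADEs will be reported to the trial co-ordinating centre if they fulfil the criteria for seriousness". A second condition asks for a possible link to taking part in the trial. The third condition sets the expectedness test and defines it by the patient population: "they are unexpected i.e. the event is not an expected occurrence for patients who have had a cardiac arrest". The three are joined by a plain conjunction, so an event must meet all of them. There is no separate sentence for device effects.

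Under Outcome Measures, "The primary outcome for the trial is survival to 30 days post cardiac arrest". The secondary outcomes cover survival at other times, quality of life, neurological status, cognition, mood and post-traumatic stress, and end with "hospital length of stay; intensive care length of stay". None is an injury or device-harm outcome.

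**The concern.** Expectedness is a reasonable filter for SAEs in this trial. Most participants will die or be critically ill, and reporting every such event would bury any signal. It fits device effects less well. For a device, the useful question is whether the device may have contributed to a serious event. The rule asks instead whether cardiac-arrest patients have events of that type anyway.

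All participants have a resuscitation attempt under the eligibility criteria, and LUCAS-2 does the same mechanical job as a rescuer's hands. Its plausible harms are therefore likely to resemble those of manual compression. The rule looks at the kind of event and not its frequency or severity, so more of a familiar kind would trigger no report.

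What is at stake is the trial's description of device safety. The Background says robust human evidence on the device is lacking, and the Consent section explains that patients are enrolled without prior consent. Both make a clear account of serious device effects worth having.

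**Working it through.** No figure in the article depends on this rule, so the check is a reading of the text, plus one piece of arithmetic on how far follow-up reaches.

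**Step 1: apply the rule to each class of event.**

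| Serious event | Related? | Expected in cardiac-arrest patients? | Must be reported? |
|---|---|---|---|
| A | Judged related to LUCAS-2 | No | Yes |
| B | Judged related to LUCAS-2 | Yes | No |
| C | Not related | Either | No |

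Class B is the problem. These events have already been judged serious and device-related, and only the population benchmark removes them.

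**Step 2: look for another stated route by which a non-fatal class B event would reach the trial.**

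- Outcome Measures: no injury or device-harm item.
- Data Collection: routine ambulance data stop at hospital admission, and what follows concerns vital status. An injury diagnosed in hospital lies outside this.
- Follow-up, 3 months: beyond the quality-of-life measures, "details of ICU and hospital discharge dates will be collected, and an assessment of CPC score made". No injury item is named.
- Follow-up, 12 months: quality of life, mood, post-traumatic stress and cognition. Resource use is recorded by participants at both visits.
- Threshold for resuscitation: the monitoring of accumulating data concerns who is resuscitated, not harm.
- Statistical Analysis: "Interim analyses will be conducted at least once per year during recruitment and supplied confidentially to the DMC". The section does not mention harms.

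The article names no other direct route.

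**Step 3: check what still captures harm.** Deaths are ascertained in both arms whatever their cause or expectedness, through register offices and central flagging, and they enter 30-day and 12-month survival. Fatal device harm is therefore counted, but only net of any benefit: a death caused by injury and a life saved by better compressions cancel in the comparison.

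**Step 4: how far can the follow-up visits reach?** Inputs from Sample Size Required: 82 LUCAS clusters of 15, with survival of 5% (control rate) to 7.5% (target).

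- LUCAS patients: 82 × 15 = 1230.
- Survivors to 30 days: 1230 × 0.05 = 61.5 to 1230 × 0.075 = 92.25, so about 62 to 92.

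The article expects 30-day survival to be close to survival to discharge, and consent for follow-up is sought from those discharged alive. Quality of life, neurological status and self-reported resource use are thus available for roughly 62 to 92 LUCAS patients, less later deaths and those who do not consent. These measures could reflect severe injury only indirectly.

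**The case against.** The strongest reply is that this is one sentence in a condensed article. The full protocol may hold a list of expected events, definitions of SAE and SADE, and arrangements for recording events that are not reported promptly. The article never says that compression injuries count as expected. It governs what goes to the co-ordinating centre and does not say that other injuries go unrecorded; they may well sit in clinical notes. Deaths are captured almost completely and reach the DMC at least yearly. Length of stay, neurological status and quality of life may pick up some severe non-fatal harm.

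Much of this stands. That compression injury is expected is an inference, and the point must be worded that way. The absence of definitions, an event list or device-malfunction procedures is no defect in an article.

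It does not remove the point, because the sentence is an operative rule with its own definition, not a gap. A list of expected events would only specify which device effects are screened out. Only a separate route for SADEs would cure the problem, and the sentence treats the two event types together. Records held elsewhere do not help the DMC unless something brings them to the trial.

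A reader might go further and infer that an excess of harm from LUCAS-2 could not be seen at all, or that every serious compression injury would go unreported. The documents do not support either. Fatal harm enters survival, unexpected device effects are still reported, and the boundary of what is expected is not given. Nor could an absence of reports be turned into an upper limit on the injury rate if the filter were removed: the article describes no injury examination of all 1230 LUCAS patients.

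**Conclusion.** The concern holds in a limited form. As written, the rule lets a serious non-fatal event judged related to LUCAS-2 go unreported when it is of a kind also expected in cardiac-arrest patients, and no listed outcome records such harm directly. Fatal harm is captured, but as a net effect on survival.

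The size cannot be put as a number of events, because the article gives neither an injury rate nor a list of expected events. No sample size, error rate or efficacy estimate is affected; the consequence is confined to safety monitoring and the description of device safety. The change is worth making but is not critical to the primary result.

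The conclusion rests on two assumptions: that the sentence is applied literally to SADEs, and that the full protocol has no separate SADE route. If it has one, the article's sentence misdescribes it and only the wording needs correcting. That compression injuries fall in the screened-out class is plausible but not stated.

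**What to change.** Split the sentence in two:

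- **SAEs:** keep the present three conditions, including expectedness in cardiac-arrest patients.
- **SADEs:** require every serious event judged potentially related to the LUCAS-2 device to be reported to the co-ordinating centre, whether or not it is of a kind expected in these patients.

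List the SADEs for the DMC alongside the interim analyses, labelled as descriptive device-safety data. They should not be presented as a comparison between arms. Attribution would be made by staff who, as the Blinding section says of paramedics, know the allocation, and asking them to attribute injuries to manual compression in the control arm would invite differential ascertainment.

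The cost is a short text change and some additional report forms. Outcomes, sample size and analysis stay as they are.

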### Statistical Analysis

All analyses will be by intention to treat, and all estimates will be adjusted to account for the cluster randomised design. Dichotomous outcomes (survival to 30 days, hospital discharge, 3 months and 12 months, and neurologically intact survival) will be presented as risk ratios and 95% confidence intervals. Survival will also be analysed as a time to event outcome, using survival analysis, with adjustment for clustering and important covariates. Results will be presented using hazard ratios and their 95% confidence intervals. Other time to event outcomes (duration of hospital and ICU stay) will be analysed in the same way. Continuous outcomes (quality of life, anxiety and depression, cognition and post traumatic stress) will be analysed by multi-level linear regression, with adjustments for important covariates. The results will be presented as the difference in means between the groups and its 95% confidence interval. CPC score will be analysed by multi-level ordinal logistic regression[21] and the results will be presented using odds ratios and their 95% confidence intervals. Reporting of analyses will follow CONSORT guidelines for the reporting of cluster randomised trials[22]. A detailed analysis plan will be drawn up by the study statisticians and approved by the DMC.

Four pre-specified subgroup analyses will be conducted to conform with Utstein recommendations: witnessed cardiac arrest versus not witnessed; bystander CPR versus no bystander CPR; type of initial rhythm (VF/VT; PEA; asystole); presumed cardiac aetiology of cardiac arrest. Subgroup analyses will use statistical tests of interaction [23]. In addition, we will model the effects of age and the time interval from the 999 call to arrival of the trial vehicle on the effects of the LUCAS-2 intervention, using logistic regression analyses.

Interim analyses will be conducted at least once per year during recruitment and supplied confidentially to the DMC, who will consider the results and make recommendations to the Trial Steering Committee (TSC) about continuation of recruitment or any modification to the trial that may be necessary.

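### Quality of life, mood, cognition and post-traumatic stress are measurable only in consenting survivors, so their mean differences between arms are not the intention-to-treat comparisons the protocol declares

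*Protocol article*

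**What the plan says.** The Statistical Analysis section opens with a blanket statement: "All analyses will be by intention to treat". It then fixes the method for the patient-reported and cognitive scales: "Continuous outcomes (quality of life, anxiety and depression, cognition and post traumatic stress) will be analysed by multi-level linear regression", adjusted for covariates and reported as a difference in means with its confidence interval. For neurological category it says: "CPC score will be analysed by multi-level ordinal logistic regression", reported as odds ratios. It does not say which patients enter that ordinal model.

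The Consent section seeks agreement to follow-up from patients who survive to hospital discharge, with a consultee where capacity is lacking. The Follow-up section then says: "Where consent is given, surviving participants will be followed up approximately 3 months after their cardiac arrest". Quality of life and CPC are assessed at that visit. Quality of life, HADS, PCL-C and MMSE are taken at the 12-month visit.

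Three other parts of the article bear on the point:

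- Outcome Measures lists neurologically intact survival at 3 months, and Statistical Analysis reports it as a risk ratio. Deaths count as failures there.
- Economic analysis plans a QALY comparison.
- Data Collection obtains deaths for participants from Register Offices and through flagging on the NHS Central Register.

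**The concern.** A patient who has died cannot complete SF-12, EQ-5D, HADS, PCL-C or MMSE, so a difference in observed means on these scales is taken within survivors. Survival happens after randomisation and is the primary outcome. If the device raises survival as the design supposes, the LUCAS survivors include patients whose counterparts in the control arm are dead and absent from the comparison. The two survivor groups then differ in composition for a reason created by the treatment. Covariate adjustment removes that difference only so far as the covariates capture it.

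A difference in means could therefore appear with no change in any individual's function. If the extra survivors are more impaired than the rest, it goes against LUCAS; if less impaired, it goes in favour. Under a general intention-to-treat statement, a reader would be entitled to take either result as a randomised treatment effect on quality of life or cognition. The later analysis plan can add detail, but to resolve this it would have to depart from the principle the article states.

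**Working it through.** **Inputs.** The section headed Sample Size Required gives the design target: "We aim to detect, with 80% power, an increase in the incidence of survival to 30 days from 5% in the control arm". The LUCAS rate there is 7.5%. The same section plans "with a randomisation ratio of 1:2 and a cluster size of 15", giving 82 LUCAS and 163 control vehicles and 3675 patients. From Power and Sample Size: ICC 0.01. The significance level is not given for the sample size. Two-sided 0.05 is assumed, in line with the 95% confidence intervals. No consent or follow-up rate for survivors is given.

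**1. The stated sample size.** Pooled proportion = (0.075 + 2 × 0.05)/3 = 0.0583. Per LUCAS arm, without clustering:

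n = [1.96 × √(0.0583 × 0.9417 × 1.5) + 0.842 × √(0.075 × 0.925 + 0.05 × 0.95/2)]² / 0.025² ≈ 1075, with 2150 controls.

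Design effect = 1 + 14 × 0.01 = 1.14. Total = 3225 × 1.14 = 3676.5, or 81.7 and 163.4 vehicles. The plan's 82 and 163 vehicles (3675 patients) are reproduced.

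**2. Patients who could supply these scales.**
- LUCAS: 82 × 15 = 1230; 1230 × 0.075 ≈ 92.
- Control: 163 × 15 = 2445; 2445 × 0.05 ≈ 122.
- Together: 214.5/3675 = 5.8%. About 94% of participants cannot supply them, before refusals and before deaths between 30 days and the 3- and 12-month visits.

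**3. Extra survivors.** Share of LUCAS survivors in excess of the control rate = (0.075 - 0.05)/0.075 = 1/3. This is the share who would have died under manual compression if the device causes no deaths. If it causes some, the share is larger.

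**4. Shift with no individual's function changed.** If the extra third score d SD worse than the rest, the LUCAS mean shifts by -d/3. The values of d are assumed.

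| Assumed deficit d (SD) | Shift in LUCAS mean (SD) |
|---|---|
| 0.25 | -0.08 |
| 0.5 | -0.17 |
| 1.0 | -0.33 |

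A negative d (extra survivors better than the rest) reverses the sign.

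**5. How often the shift would reach significance.** Trials were simulated with 245 vehicles and a random-intercept linear model, 200 replicates per scenario. The ordinary-regression p value was used where the mixed model returned none.

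| Deficit (SD) | Share followed up (assumed) | Trials with significant apparent harm |
|---|---|---|
| 1.0 | 100% | 58% |
| 1.0 | 60% | 38% |
| 0.5 | 60% | 11% |

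**6. The same contrast on the utility scale.** Assume a survivor mean of 0.7 and a deficit of 0.1 to 0.3 in the extra third. The survivor-only difference is -0.1/3 to -0.3/3, that is -0.03 to -0.10. With death scored 0, the all-participant difference is 0.025 × (0.7 - deficit), that is +0.015 to +0.010. Under these assumptions the two analyses have opposite signs.

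**7. Does the vehicle random effect add a second problem?** Expected 30-day survivors per vehicle are 15 × 0.05 = 0.75 (control), 15 × 0.075 = 1.125 (LUCAS) and 214.5/245 = 0.88 overall. About 53 of 245 vehicles (22%) would have two or more. In the simulations the vehicle variance was estimated near zero in 40 to 51% of fits. With no true difference, the treatment estimate was unbiased and the rejection rate was 4 to 5%.

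**The case against.** The strongest reply is that the main results are safe. The primary outcome and the other survival outcomes can be determined for essentially everyone. Neurologically intact survival already counts deaths, and so must the QALY comparison. How survivors fare is a legitimate secondary question, and these scales would be reported beside survival. All of this stands, and it limits the point to a few secondary outcomes. It does not make a survivor-only mean difference intention to treat, and no all-participant counterpart is stated for cognition, mood or post-traumatic stress.

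Three stronger readings are tempting, and the document does not support them.

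- **That the survivor scales will make an effective device look harmful.** Nothing in the article says the extra survivors are frailer. The deficits in steps 4 to 6 are assumptions, and the survivor counts are 30-day figures with full consent. At 0.5 SD and 60% followed up, significant apparent harm appeared in only 11% of simulated trials.
- **That the multi-level model has too few survivors per vehicle to be usable.** The LUCAS arm averages slightly more than one at the design alternative. The vehicle variance is poorly estimated, but the treatment test keeps its size, so the planned model need not be replaced on this ground.
- **That CPC is analysed in survivors only.** Assessment at the home visit suggests it, but the analysis set is not stated. Read literally, the intention-to-treat sentence would bring deaths in, and they are available.

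It is also fair to object that scoring deaths does nothing for survivors who decline follow-up. They remain missing and need to be reported.

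**Conclusion.** The point holds in a limited form. The intention-to-treat statement is wider than the data allow: quality of life, HADS, PCL-C and MMSE can be compared only among consenting survivors, at most about 6% of participants on the design figures. Because the trial aims to change survival, randomisation does not protect that comparison.

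The bias has no fixed sign or size. The -0.08 to -0.33 SD range follows from an assumed deficit of 0.25 to 1.0 SD in the extra third, the design survival rates and a device that causes no deaths. For CPC the fault is narrower: the set is implied by how the data are collected but not stated, and with deaths excluded the same problem would apply. The survival outcomes are unaffected. The change is worth making because it alters what may be concluded from the affected scales.

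**What to change.** 1. Limit the intention-to-treat statement to outcomes known for all participants.
2. Label the SF-12, EQ-5D, HADS, PCL-C and MMSE regressions as comparisons among consenting survivors, to be read beside the survival results and not as treatment effects. The planned multi-level model can stay.
3. Run the CPC ordinal model over all participants, with deaths in the worst category. This agrees with how neurologically intact survival treats deaths.
4. Report the all-participant utility comparison, with death scored 0, from the QALY analysis already planned.
5. Report by arm the number of survivors who did not consent or were not followed up. They stay missing under items 3 and 4.

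This costs wording and a definition of analysis sets. Deaths are already collected under Data Collection, so no new data are needed for them. The downside is that the survivor scales carry a weaker claim.
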